### Statistical analyses

Analysis will be descriptive statistics, *t*-tests comparing means, chi square analysis of frequency data and ANOVA analyses. Evaluable data and intention to treat analysis will occur. Results will be analysed and interpreted using SPSS. The majority of the results will be simple descriptive data summarising take-up, completion and drop-out rates. Finally, the PHQ-9 data will be used to perform a power calculation for the future large RCT.

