### Aims

The aim of this study is to recruit Chinese-speaking international students based in the West of Scotland and experiencing symptoms of depression and/or anxiety. We will include both those diagnosed with depression as well as those with raised mood scores without a formal diagnosis.

In this pilot study, the main aim will be to investigate take-up, drop-out and completion rates of the online course and the completion rates for data collection.

Secondary outcomes will be mood ratings at 3 months. We will use changes in the Patient Health Questionnaire 9 (PHQ-9) [13] score to provide data relating to the effect of the intervention on depression levels. The PHQ-9 is our chosen primary outcome measure for the future substantive RCT and provides a valid and reliable measure of depression. It will provide an indication of efficacy and, together with the drop-out/retention rate, will be used to provide a power calculation for the future larger RCT; providing evidence that a change in depression levels between the intervention and control groups can be observed. This is an unfunded PhD study to establish viability of applying for a substantive later funded RCT.

The specific research questions of the study are outlined below.

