## Methods/design

### Overview

This is a pilot study with a randomised controlled design. This study will investigate the possibility of delivering the culturally adapted Living Life online life skills resource to Chinese-speaking international students. In this RCT, 50 % of participants will be randomly allocated to receive immediate access (IA) to the Living Life (LL) online intervention and 50 % will be in the delayed access control group (DA). The primary end point is 3 months at which point the control arm will be invited to begin the intervention. A further follow-up point will be at 6 months post-randomisation. This 6-month time point was chosen as a comparative, reasonable follow-up length to fit the structure of the academic year.

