### Participants

The aim is to recruit up to 50 participants in total to provide an indication of the take-up, use and impact of the course on low mood or anxiety; and identify any problems with recruitment, delivery of the intervention and completion of evaluation measures. Such problems could be recruitment difficulties, drop-out during the intervention, poor adherence to the online course and failure to complete follow-up measures.

Inclusion criteria:

To enter the study, individuals must be Chinese-speaking (Mandarin or Cantonese) international students aged 18 years of age or more, registered as students (undergraduate or postgraduate) at the University of Glasgow and living in the UK for the next 2 months. This is to ensure they are in the UK when using the intervention so that appropriate support can be offered in the event of identified risk. Current symptoms of depression with the score 5+ on the PHQ-9 [13] depression questionnaire and/or a score of 5+ on the generalised anxiety disorder −7 (GAD-7) [14] scale (Chinese language versions) must be present for eligibility. Participants will be required to have broadband web access and also be willing and able to use the online course.

Exclusion criteria:

Participants will be excluded if they do not fulfil the inclusion criteria or are currently receiving specialist mental health treatment or current psychotherapy/counselling. Students who are on antidepressants will not be excluded, but we will record the drug, dose and length of time on the medication.

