### Follow-up data collection

The main follow-up point will be at 3 months with an additional follow-up assessment at 6 months (see Table 1). The primary outcome in the future substantive study will be PHQ-9 at 3 months.

**Table 1 Tab1:** Timing of measures taken during the study

Baseline	3 months	6 months
Demographic data	PHQ-9	PHQ-9
PHQ-9	GAD-7	GAD-7
GAD-7	WSAS	WSAS
WSAS	CSQ-8 (IA group only)	CSQ-8 (DAC group only)

Baseline measures include age, gender, course type (undergraduate/post-graduate), ethnicity, mood, anxiety, social function, (Chinese versions where available), antidepressant medication and current psychiatric treatment.

The following measures will be completed online:

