### Knowledge added to the literature

In the pilot study, the sample sizes are chosen to provide the information required. They are deliberately not informed by a power calculation as the purpose of this study is to provide the information required to test delivery of the components of the study and to provide a power calculation for a future substantive study. Moreover, the primary outcome will be the take-up, drop-out and completion rates of the online course and the collection rates for data. Secondary outcomes will be mood rating scales using descriptive statistics. We will use changes in PHQ-9 score to provide an impact of effect of the intervention on mood at 3 months, which will be the primary outcome for the future substantive RCT.

In addition, the results of the current study relating to changes in PHQ-9 and GAD-7 scores could inform and guide practitioners about the mental health needs of Chinese international students and the difficulties faced when they study overseas [3].

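### The named mood comparisons (t-tests, ANOVA, change in PHQ-9) do not adjust for the baseline scores collected; ANCOVA would be more precise at no data cost

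*Protocol article*

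**What the plan says.** Statistical analyses (Methods/design) names descriptive statistics and t-tests "comparing means, chi square analysis of frequency data and ANOVA analyses". It does not say which outcome each test is for and names no covariate. It adds that the PHQ-9 data will feed the power calculation for the main trial.

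The effect measure is fixed elsewhere. Knowledge added to the literature (Discussion) says: "We will use changes in PHQ-9 score to provide an impact of effect of the intervention on mood at 3 months". Aims also relies on changes in PHQ-9 and says of that measure: "It will provide an indication of efficacy and, together with the drop-out/retention rate, will be used to provide a power calculation".

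Baseline values exist. Follow-up data collection lists "ethnicity, mood, anxiety, social function" among the baseline measures, and Table 1 shows PHQ-9, GAD-7 and WSAS at baseline, 3 months and 6 months.

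On size and design, Participants states: "The aim is to recruit up to 50 participants in total". Overview gives equal allocation, and Randomisation rules out stratification.

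On how mood will be reported, Knowledge added to the literature says: "Secondary outcomes will be mood rating scales using descriptive statistics".

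**The concern.** The 3-month PHQ-9 comparison is secondary here, but it is the planned primary outcome of the main trial, and research question d asks the pilot how large that trial must be. The analysis named for it makes poor use of information already collected.

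A t-test on 3-month scores discards the baseline. A change score uses it, but subtracts it in full when only part of a baseline difference is expected to persist. In a small unstratified trial, a chance baseline difference is therefore carried into the first contrast and over-corrected in the second. Both give wider intervals than ANCOVA, and an SD taken from either would make the main trial larger than an ANCOVA analysis requires.

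Separately, one section lists significance tests while another says mood scales will be described, so the status of any p-value on them is unclear.

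**Working it through.** **Which outcomes the tests concern.** By Table 1, the scales measured in both arms at the same time are PHQ-9, GAD-7 and WSAS. CSQ-8 is given to one arm at each time point, and take-up, drop-out and completion are mainly rates. The tests of means therefore fall most naturally on the mood and function scales. This is an inference, since the article does not assign them.

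**Inputs.** From the article: up to 50 participants at equal allocation, so 25 per arm before attrition. It states no alpha, power, SD, effect size or correlation for this comparison, so there is no figure of its own to reproduce. Assumed: baseline-to-3-month correlation rho from 0.3 to 0.7, equal SD at both times, standardised effect d = 0.5 in units of that SD, two-sided alpha 0.05 and 80% power. The formulas use the normal approximation and ignore the one degree of freedom ANCOVA spends on the covariate.

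**Variance factor f, relative to a follow-up-only t-test.**
- Follow-up only: 1
- Change score: 2(1 − rho)
- ANCOVA: 1 − rho²

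The ratio of ANCOVA to change score is (1 − rho²) / [2(1 − rho)] = (1 + rho)/2.

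| rho | f, change | f, ANCOVA | ANCOVA / follow-up | ANCOVA / change |
|---|---|---|---|---|
| 0.3 | 1.40 | 0.91 | 0.91 | 0.65 |
| 0.5 | 1.00 | 0.75 | 0.75 | 0.75 |
| 0.7 | 0.60 | 0.51 | 0.51 | 0.85 |

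Below rho = 0.5 the change score is less precise than ignoring baseline altogether.

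**Precision in this pilot.** The 95% half-width is 1.96 × sqrt(2f/25), in SD units.

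| rho | Follow-up only | Change | ANCOVA |
|---|---|---|---|
| 0.3 | 0.55 | 0.66 | 0.53 |
| 0.5 | 0.55 | 0.55 | 0.48 |
| 0.7 | 0.55 | 0.43 | 0.40 |

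If 20 per arm were analysed (an assumed 20% loss), the rho = 0.5 row would read 0.62, 0.62 and 0.54. The variance ratios do not depend on the number analysed.

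**Chance imbalance.** With 25 per arm, the standard error of the baseline difference is sqrt(2/25) = 0.28 SD. An imbalance of that size shifts the follow-up contrast by rho × 0.28 = 0.08 to 0.20 SD as rho goes from 0.3 to 0.7. It shifts the change contrast by (1 − rho) × 0.28 = 0.20 to 0.08 SD in the opposite direction.

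**Size of the future trial.** n per arm = 2 × (1.960 + 0.842)² × f / d², which is 62.8 × f at d = 0.5, rounded up.

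| rho | Follow-up only | Change | ANCOVA |
|---|---|---|---|
| 0.3 | 63 | 88 | 58 |
| 0.5 | 63 | 63 | 48 |
| 0.7 | 63 | 38 | 33 |

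At d = 0.3 and rho = 0.5 the figures are 175, 175 and 131.

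**The case against.** The strongest reply is that the article never says the comparisons are unadjusted. It lists families of tests, and covariates are often left to an analysis plan that is not shown. ANOVA could mean a repeated-measures model, and a change score does use the baseline. Part of this stands: the absence of adjustment is inferred from the methods named, and it would be wrong to say baseline is ignored throughout. It does not remove the point, because the article itself fixes both the tests and the change score. With baseline and 3 months, the arm-by-time test in a repeated-measures ANOVA is the change-score comparison again.

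It can also be said that all three estimators are unbiased under randomisation, so this is a matter of efficiency. That is correct. The imbalance figures describe what happens given a particular imbalance, not a bias on average, and the gain is small if rho is low: at rho = 0.3 the half-width moves only from 0.55 to 0.53 against the follow-up t-test.

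Three stronger readings are tempting, and the document does not support them.
- A reader might infer that the Discussion limits mood outcomes to description alone. It does not exclude tests, and Statistical analyses itself puts descriptive statistics first. The mismatch is one of wording.
- Because entry requires a score of 5 or more on PHQ-9 and/or GAD-7, a reader might infer that regression to the mean distorts the result. Both arms meet the same entry rule, so it does not bias the between-arm comparison, and no section plans to read within-arm change as the treatment effect.
- A reader might infer that the residual SD for the main trial cannot be obtained. Both scores are collected, so it can be computed. An unadjusted SD would make the main trial conservative in size, not invalid.

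**Conclusion.** The point holds as a worthwhile improvement in efficiency, not as an error that invalidates the pilot. The primary aim is feasibility, and no feasibility conclusion depends on it. Its weight comes from the PHQ-9 power calculation, a stated output of the study.

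ANCOVA is more precise than both named approaches at every correlation considered. The example of 48 rather than 63 per arm is a saving of 15 per arm, or 30 in total. The correlation, the effect size and equal SDs are assumptions. The variance ratios do not depend on the effect size, but the absolute numbers do. The conflict between planned tests and descriptive reporting of mood is minor and needs only a clarifying phrase.

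**What to change.** In Statistical analyses, state that the 3-month between-arm difference in PHQ-9, and likewise in GAD-7 and WSAS, will be estimated by ANCOVA with the baseline value of the same scale as covariate, and reported with a 95% confidence interval. Add that the SD, the residual SD and the baseline-to-3-month correlation of PHQ-9 will be reported as inputs to the power calculation. Bring the references to change in PHQ-9 in Aims and in Knowledge added to the literature into line with this.

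To settle the smaller point, say in Statistical analyses that any significance tests on mood scales are exploratory, and make the Discussion sentence on descriptive statistics agree.

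The cost is a few sentences of text and one degree of freedom per model. No new data are needed, and the model is standard in SPSS, the software already named.

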## Discussion

### Importance of the project

We have recently completed a systematic review of the use of low-intensity CBT interventions (online or book-based) with Chinese-speaking populations (manuscript in preparation). This found no previous evaluations of such cCBT treatments aimed at Chinese-speaking international students. Liu’s [3] study of mental health problems in Chinese international college students found that depression is significant in this group, and that access to help in the appropriate language can be limited within English-based student counselling and NHS services. The current pilot study will help inform whether an online low-intensity CBT approach that would increase access to treatment can be evaluated in this population and help define the sample size required to answer the question of clinical effectiveness.

### Knowledge added to the literature

In the pilot study, the sample sizes are chosen to provide the information required. They are deliberately not informed by a power calculation as the purpose of this study is to provide the information required to test delivery of the components of the study and to provide a power calculation for a future substantive study. Moreover, the primary outcome will be the take-up, drop-out and completion rates of the online course and the collection rates for data. Secondary outcomes will be mood rating scales using descriptive statistics. We will use changes in PHQ-9 score to provide an impact of effect of the intervention on mood at 3 months, which will be the primary outcome for the future substantive RCT.

In addition, the results of the current study relating to changes in PHQ-9 and GAD-7 scores could inform and guide practitioners about the mental health needs of Chinese international students and the difficulties faced when they study overseas [3].

### Benefits to participants

Participation within this research will allow Chinese-speaking international students who are experiencing symptoms of anxiety and depression to take part in an online CBT-based course for stress and low mood in their own language. There is evidence supporting the use of the CBT self-help approaches for depression and anxiety by teaching problem-solving skills, assertiveness, tackling negative thinking and increasing activity levels [11, 12, 24, 25]. By using the package, it is hoped that participants may learn new skills to help with symptoms of low mood, anxiety or depression. The satisfaction data will help us to gain a key insight into how online websites can be best delivered and supported in this setting.

Little previous research has examined the presence of adverse impacts of using cCBT. We are therefore monitoring progress using support contacts and in addition have added a question at follow-up to examine adverse consequences in the IA arm. It is unlikely that participants’ condition will worsen significantly during the study. We do however have risk management protocols in place if needed, as outlined in the following section.

### Ethical considerations

There are a number of ethical considerations that have been taken into account in the preparation of this protocol. These are as follows:

#### Recruitment

Recruitment into the study will involve self-referral via web links from established websites, through a project-specific recruitment site, via email, posters and via advertisements. This will involve liaison and support from the University of Glasgow Counselling service, and the University Chinese Society. No individuals will be recruited from NHS sites.

#### Consent

We will be recruiting only participants who are aged 18 years or over. Informed consent will be obtained from all participants prior to them entering the study. Participants will have the opportunity to ask questions about the study before being asked to complete the consent form. Participants will only be given access to the intervention once eligibility has been established and informed consent given.

#### Risk management

The Participant Information Sheet will give suggestions for sources of additional/urgent support including their GP, NHS24, student counselling, A + E and Samaritans. Additionally, the study website contains a tab detailing sources of urgent help. Finally, all participants will be assigned a Chinese-speaking support worker based at the University Student Counselling who will contact them each week to monitor their progress. Therefore, participants will have the opportunity to discuss any deterioration in their mood, in which case the support worker would inform the clinical lead of the study, CW.

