### Immediate access (IA) group

Participants randomised to IA will be given log in details for the LL online intervention and will begin receiving weekly support via automated emails in either Mandarin or Cantonese. In addition, personalised short weekly support sessions will be offered by email from a Chinese-speaking counsellor. Support will focus on encouraging module completion and practicing what has been learned. Copies of emails will be retained to check adherence to the Plan, Do, Review model [15] of support. This model uses two worksheets (planner and review sheets) to apply what is learned in practice.

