### Delayed access control (DA) group

Participants randomly allocated to the delayed access group will be informed that they will be given access to the online course after a delay of 3 months. As in the IA group, all participants will continue with any usual treatment as required.

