### Cultural adaptations

Simple/traditional Chinese, Mandarin and Cantonese versions of the materials have been made available. A series of facilitated focus groups identified changes required to culturally adapt content for use with this target population. The main finding from the focus groups was that participants felt that all of the research materials (including advertisements and questionnaires) and the online intervention should be written in the Chinese language. The modules were already in Chinese but all of the menu items and any written information on the home page had to be translated. Additionally, English language versions of the modules were removed from the website.

Opinions relating to preferred support were also collected during the focus groups. The majority of participants in the focus groups stated that support sessions delivered via email would be acceptable and in most cases preferable to telephone support. Therefore, the support sessions will be delivered by a support worker based at the student counselling service via weekly emails to participants. These emails will be written in Chinese, as this was expressed as important by participants.

Finally, the layout of the website was adapted following comments from the focus group participants. The full results of the focus group study will be published separately.

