### Support

Participants will have the option to sign up to receive weekly automated support emails with the option of traditional or simple Chinese script. As recommended by the focus group work, participants will receive a regular personalised support element; delivered by a Chinese-speaking trained counsellor via email. This will test the support offered for use in the later substantive RCT.

The support is protocol driven and focused on encouraging use and application of the intervention. It is designed to encourage an individualised plan to be made at the end of each session using a Plan, Do, Review structure, with a focus on making changes in their lives and using the materials to support them in doing this. Therefore, the online intervention uses a structured, guided self-help approach that may be appealing to students.

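### The adverse-consequences question omits the delayed arm's later course use, and the plan should settle whether that arm has weekly support-worker contact before 3 months

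*Protocol article*

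**What the plan says.** **Harm question.** The section on the Client Satisfaction Questionnaire (CSQ-8) ends with a list of extra checks at 3 months. One of them covers adverse consequences of using the site, and it is confined to the IA arm. Benefits to participants, in the Discussion, repeats that restriction. It also says that little research has looked at adverse effects of computerised CBT, and it names support contacts as a further means of monitoring.

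**Course use by the delayed arm.** The Overview sets the primary end point at 3 months, "at which point the control arm will be invited to begin the intervention". Table 1 (Follow-up data collection) gives the CSQ-8 to the IA arm at 3 months and to the delayed arm at 6 months.

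**Weekly contact.** Risk management says that "all participants will be assigned a Chinese-speaking support worker based at the University Student Counselling who will contact them each week", and that through this contact "participants will have the opportunity to discuss any deterioration in their mood, in which case the support worker would inform the clinical lead". Three other sections describe weekly contact of the same kind:
- Cultural adaptations: "the support sessions will be delivered by a support worker based at the student counselling service via weekly emails to participants".
- Immediate access (IA) group: "personalised short weekly support sessions will be offered by email from a Chinese-speaking counsellor".
- Support: "The support is protocol driven and focused on encouraging use and application of the intervention".

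The section on the Delayed access control (DA) group says only that these participants "will be informed that they will be given access to the online course after a delay of 3 months", and that usual treatment continues. Randomisation states that follow-up after allocation is identical in the two groups.

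**The concern.** Two groups will use the course: the IA arm from entry and the delayed arm from 3 months. Satisfaction is collected from both and harm from one. For a pilot that itself points to the thin evidence on harm, this discards up to half of the available answers, from people who already receive a form at the right time. The restriction to one arm is stated in two places, so it is not a detail lost in condensing a longer protocol.

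The second issue is smaller. Risk management gives weekly contact to everyone, while the sections that describe the contact tie it to using a course that the delayed arm does not have for 3 months. A reader cannot tell whether delayed-arm participants have the support-worker route to the clinical lead in that period. Nor can a reader tell whether the comparator is a passive wait or a wait with weekly personal contact. That affects how the 3-month PHQ-9 difference is read when it informs the sample size of the later trial.

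**Working it through.** The plan gives no figure for either issue, so there is none to reproduce.

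**1. Who is asked about harm, and when**

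| | IA arm | Delayed arm |
|---|---|---|
| Course offered | 0 months | 3 months |
| CSQ-8 (Table 1) | 3 months | 6 months |
| Offer to CSQ-8 | 3 − 0 = 3 months | 6 − 3 = 3 months |
| Adverse-consequences question | 3 months | none described |

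The intervals match from the offer of access. Actual start dates may differ, since the delayed arm is only invited to begin.

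**2. What the omitted answers are worth**

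Inputs: up to 50 participants (Participants section), half to each arm (Overview), so 0.50 × 50 = 25 per arm. If n people answer and none reports a harm, the one-sided 95% upper limit on the true rate is 1 − 0.05^(1/n).

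| Answers n | Basis | Upper limit |
|---|---|---|
| 25 | IA arm only, all use the course and answer | 1 − 0.05^(1/25) = 11.3% |
| 50 | both arms, all use the course and answer | 1 − 0.05^(1/50) = 5.8% |
| 37 | 25 IA + 12 delayed-arm users (assumed take-up) | 1 − 0.05^(1/37) = 7.8% |
| 20 | IA arm only, 20% non-response (assumed) | 1 − 0.05^(1/20) = 13.9% |
| 40 | both arms, 20% non-response (assumed) | 1 − 0.05^(1/40) = 7.2% |

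The documents give neither delayed-arm take-up nor non-response, so the last three rows only show a range. Adding the delayed arm roughly halves the limit at best (11.3% to 5.8%). With about half of that arm using the course it still falls to 7.8%.

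**3. Whether the delayed arm has weekly contact before 3 months**

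- For: Risk management says all participants, with no limit by arm or date, and gives monitoring of progress as the purpose. Randomisation says the groups are followed up identically, though this may mean outcome assessment only.
- Against: the weekly personalised emails appear under the IA heading. Cultural adaptations identifies the counselling-service worker's weekly emails with the support sessions, and Support gives their purpose as use of the intervention. The DA section mentions no contact.
- Neutral: Cultural adaptations and Support speak of participants without naming an arm.

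The text does not settle the matter, and either answer requires an edit. If the delayed arm is contacted weekly, the DA section leaves out part of the control condition. If it is not, Risk management promises more than is delivered.

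**The case against.** On harm, the question is placed at the main end point, for the arm that has the course during the randomised comparison. Later use by the delayed arm has no control group, and support contacts could bring harms to light if that arm then receives the same guided package. The plan sets no precision target for harms, so the omission is not an error in that sense. This is fair as far as it goes. But answers in the IA arm are also simply reports from users, and support contacts do not replace putting the same question to everyone who used the course.

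On weekly contact, the defence is stronger. Risk management is an express statement, and the DA section is merely silent. No section denies the delayed arm contact, and one worker can both monitor and coach.

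A reader might go further and infer that the delayed arm has no safeguard for 3 months. The documents do not support that. Read literally, Risk management includes that arm. The information sheet and website list urgent help, and usual treatment continues.

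A reader might also note that entry requires "Current symptoms of depression with the score 5+ on the PHQ-9" or a similar anxiety score, with no upper limit, and conclude that severe scores would go unattended. A condensed article commonly leaves action on severe scores to a fuller risk procedure, so that cannot be concluded here.

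**Conclusion.** The main point holds as a cheap and worthwhile improvement. The harm question, as described, reaches up to 25 of up to 50 potential course users. Asking the rest would lower the zero-event upper limit from 11.3% to at best 5.8%. That assumes full recruitment, an even split, full take-up and full response; weaker assumptions give a smaller gain.

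The secondary point holds as an ambiguity between Risk management and the DA section. It does not show that a protection is absent.

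It would also be too strong to say that the PHQ-9 estimate cannot be interpreted. PHQ-9 is a secondary outcome of this pilot, behind take-up, drop-out and completion. The estimate can be read properly if the report states which control was run. The documents give no basis for saying how far weekly contact would shift it.

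**What to change.** **Harm question.** Ask the delayed arm the same adverse-consequences question at 6 months, alongside the CSQ-8 it already completes. Report the answers by arm first, then for all course users. The cost is one extra item on an existing form. The drawback is that delayed-arm answers are uncontrolled and come only from those who stay and take up the course, which is why the arms should be shown separately before pooling.

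**Weekly contact.** Reconcile the DA section with Risk management in a sentence or two, in one of two ways:
- state in the DA section that this arm receives the weekly monitoring contact, without course coaching, as part of the control condition; or
- limit the Risk management statement to course users, and state the delayed arm's route to the clinical lead before 3 months.

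The choice should reflect what is intended. If weekly contact is not already planned, adding it would take support-worker time and make the control less passive. Whichever is chosen, report which control was run when the PHQ-9 difference is used for the future power calculation.
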